### Randomization procedure

Using a double-blind procedure, we will randomly assign all of the participants to one of the four groups. The randomization scheme will be generated using the website Randomization.com (http://www.randomization.com). Randomization and follow-up assessments will be administered by independent practitioners blind to the research hypotheses and condition assignments. The G*Power software (v3.1.9.2) [35, 36] was used to compute the minimum sample size required to conduct this study. All of the participants will be assessed with the Psychological General Well-Being Index (PGWBI) [47, 62, 85] five times: (1) at admission to the clinic, (2) at discharge, (3) at 3 months follow-up, (4) at 6 months follow-up, and (5) at 12 months follow-up. Thus, the *experimental condition* is considered as a between-group variable, and *time* is considered as a within-subject variable. The a priori statistics (partial η^2^ and correlation between measures) were computed by examining previous longitudinal studies using the PGWBI in subjects with obesity [9, 65]. The a priori partial η^2^ was set to assume a value of 0.015 (small effect size) [26, 30], the type I error (α) rate was set at 0.05 (two-sided), the power (1 – β) was set at 0.95 [26], and the a priori correlation between repeated measures was set at 0.50. Finally, sphericity was assumed. G*Power showed that there is a 95% chance to correctly reject the null hypothesis of no significant effect with an overall sample of 168 participants, 42 subjects for each group.

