### Assessment procedure

According to the behavioral framework, direct measures are preferred to psychometric inventory when possible. In any case, to deepen the understanding of mechanisms of change, psychometric measures were included. Participants will be asked to complete all study measures before randomization. Follow-up repeated measures assessment will be completed on all study participants 6 weeks later (post-treatment) and at 3, 6, and 12 months follow-up.

Demographic data such as gender, age, marital status, level of education, and employment status will be assessed in order to control for these potential confounders, checking also for biological indicators of risk—obesity, according to WHO criteria, with a BMI of 30 or more [67].

Primary outcome is physical activity as assessed continuously by wearable technology. Activity trackers will collect data, by direct measurement, of daily steps, physical activity, sleep, and food journal with the self-report app connected with the wearable device. Medical data and additional diagnoses (e.g., diabetes) that may confound results will be retrieved from clinical records.

Participants in both groups will provide a history of any psychological treatment or counseling to assess potential familiarity with mindfulness and acceptance-based therapies. A range of physiological and psychological outcome measures will assess the following: modifiable risk factors and recommended lifestyle dietary habits with the Mediterranean Diet Score [73], physical exercise with the International Physical Activity Questionnaire - Short Form (IPAQ-SF) [57] and the Acceptance and Action Questionnaire for Exercise (AAQ-EX) [85]. We also collect data about psychological well-being and quality of life (PGWBI) [47, 62, 85] and psychological flexibility (AAQ-II) [4, 49], a core process directly targeted by ACT interventions and involved as a mediator for well-being [53]. Adjusted change scores for all the outcome measures will be calculated in order to assess the ability of the interventions to produce changes over time.

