### Statistical analysis

As this study combines group design with different single-case design or, more in detail, randomly assigned multiple baseline design clustered by sub-sequential recruitment. Following methodological guidelines of RCT, the implementation of statistical analysis is linked to synergies that we can not previse at this point.

Statistical analyses will be performed using the R software [86]. Preliminary analyses will be carried out to assess the assumptions of parametric statistics; in case of violations, robust methods or data transformation will be used. Direct collected data (steps, weight, etc.) will be analyzed with an ITT approach with dropouts assumed to have regained 0.3 kg per month, an assumption already used in previous studies [16]. Dropouts will be excluded from the study.

The analysis of variance (ANOVA) will be used to examine between-group differences for all the primary and secondary outcomes at all time-points, focusing on the change in the scores. Corrected effect sizes (Hedges’ *g*) and 95% confidence interval (95% CI) will be calculated for both between-group and within-group differences.

Moreover, growth curve model analysis with a group variable (between conditions) will be used to evaluate the average growth from the baseline to 12 months after treatment for all of the outcome variables as performed in previous studies [52]. Moderation and meditational analysis will be implemented as more advanced statistical models. All data analyses will be performed using the Statistical Package for the Social Sciences (version 16.0; SPSS, Inc., Chicago, IL).

In addition, considering that the present study combines different single-case designs, more detailed randomly assigned multiple baseline designs clustered by sub-sequential recruitment, and a group design following methodological guidelines of RCTs, the implementation of statistical analysis is linked to synergies that we cannot previse at this point. For the single-case design, we use a multiple-baseline procedure with the same number of data points for all the subjects assigned to a cluster. In each multiple-baseline cluster we randomly assign the length of the baseline and, consequently, of the treatment. Detailed visual inspection and graphical analysis will be use, followed by a randomization test to ensure statistical power to the visual analysis [37, 38].

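### Group comparisons use ANOVA on change scores with no named baseline covariate: valid, but less precise than baseline adjustment (25% more variance removed for the PGWBI at the plan's correlation of 0.50)

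*Protocol article*

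**What the plan says.** The Statistical analysis section of the protocol article says that ANOVA will be used to compare the groups on every primary and secondary outcome "at all time-points, focusing on the change in the scores". It names no covariate, and analysis of covariance appears nowhere in the article. The same section adds a growth curve model with a group variable, from baseline to 12 months, for all outcomes. Neither analysis is named as primary.

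The Assessment procedure section says: "Adjusted change scores for all the outcome measures will be calculated". It does not define the adjustment. It also says that participants complete all study measures before randomisation, and that physical activity measured by the wearable is the primary outcome.

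The only correlation in the article is in the sample-size text under Randomization procedure: "the a priori correlation between repeated measures was set at 0.50". That value and the effect size were "computed by examining previous longitudinal studies using the PGWBI in subjects with obesity".

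**The concern.** When a pre-randomisation baseline is available, subtracting it from the follow-up value is seldom the best use of it. Subtraction fixes the baseline coefficient at 1, whereas the coefficient that minimises the variance is the regression slope, which equals the correlation when the SDs are equal. The further the correlation lies below 1, the more precision is lost. A chance baseline difference between arms is then also over-corrected.

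At stake are wider confidence intervals and lower power in a trial that plans on a small effect and lists its small subgroups as a limitation. With 42 per arm, chance imbalance is not negligible. The reference to adjusted change scores does not settle the matter, because a reader cannot tell whether baseline adjustment is planned.

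**Working it through.** **Inputs from the article (Randomization procedure):** four arms of 42, N = 168; five PGWBI measurements; partial η² = 0.015; α = 0.05; target power 0.95; correlation ρ = 0.50; sphericity.

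**Step 1. What N = 168 stands for.** Take the repeated-measures group-by-time interaction:
- f² = 0.015/0.985 = 0.01523, so f = 0.1234.
- λ = f²·N·m/(1−ρ) = 0.01523 × 168 × 5/0.5 = 25.6.
- Degrees of freedom are 3 × 4 = 12 and (168−4) × 4 = 656.
- Power = 94.4%. With f rounded to 0.125 it is 94.98%.

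The stated figure is therefore reproduced closely (the smallest N for 95% is 173 without rounding f). The within-subject main effect (N = 124) and the between-group main effect (N = 684) do not fit. So N = 168 rests on an interaction over five measurements, not on one change-score contrast.

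**Step 2. Variance of a single follow-up contrast.** Let σ be the SD, assumed equal at baseline and follow-up. Per participant:
- Raw follow-up value: σ².
- Change score: 2(1−ρ)σ².
- Baseline as covariate: (1−ρ²)σ².
- Ratio, covariate to change: (1−ρ²)/[2(1−ρ)] = (1+ρ)/2.

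At ρ = 0.50 the change score has 2 × 0.5 = 1.00σ², the same as the raw follow-up value, so subtracting baseline gains no precision. With the covariate it is 1 − 0.25 = 0.75σ². The variance falls by 25% and the standard error by 1 − √0.75 = 13.4%. A simulation with four arms of 42 gave a variance ratio of 0.755, so estimating the slope costs very little.

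**Step 3. Range for outcomes without a stated correlation.**

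| ρ | Change (σ²) | Covariate (σ²) | Variance saved |
|---|---|---|---|
| 0.3 | 1.40 | 0.91 | 35% |
| 0.5 | 1.00 | 0.75 | 25% |
| 0.7 | 0.60 | 0.51 | 15% |
| 0.9 | 0.20 | 0.19 | 5% |

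**Step 4. Chance imbalance.** At 42 v 42 the standard error of a baseline difference is √(2/42) = 0.22 SD. A change-score contrast over-corrects by (1−ρ) times the observed difference. For an imbalance of one standard error at ρ = 0.50 that is 0.5 × 0.22 = 0.11 SD.

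**Step 5. Power, as an illustration only.** The article gives no difference in SD units for a pairwise contrast. For an assumed true difference of 0.5 SD, the standardised effect is 0.5 on change and 0.5/√0.75 = 0.577 with the covariate. Power (ρ = 0.50, noncentral t) goes from 62.0% to 74.4% for 42 v 42, and from 89.6% to 96.1% for 84 v 84 (a factorial main effect).

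**The case against.** **Baseline adjustment may already be intended.** The change in the analysis section may be the adjusted change of the Assessment procedure section. That is possible, but the adjustment is undefined and the named test is ANOVA without a covariate. If adjustment is intended, one sentence must say so; if not, the precision is lost.

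**The growth curve model may supply the gain.** It covers all outcomes and could do so. Whether it does depends on how baseline enters the model, which the article does not say; that detail may properly sit in a fuller document. But the model comes in addition to ANOVA on change and does not replace it.

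**The 0.50 belongs to the PGWBI.** This stands. A reader might carry the 25% over to every outcome, including steps. The article does not support that: it gives no correlation or SD for tracker data, and inpatient and home activity need not have equal SDs.

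**A step-count baseline before randomisation is not shown.** This also stands. Trackers are handed over at an inpatient meeting that differs by arm: in the feedback condition it is longer and includes goal setting. That condition's baseline phase is then given a random length after allocation. For the primary outcome the covariate cannot be taken as already in hand.

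**The method is not wrong.** Agreed. A reader might infer that ANOVA on change is biased or inflates the type I error. Under randomisation it does neither.

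**Conclusion.** The point holds as one of efficiency and clarity. The stated comparison is ANOVA on change with no named baseline covariate, and the mention of adjusted change scores elsewhere does not clearly supply one. For the PGWBI, adjustment would cut the variance of a single follow-up contrast by 25%, on the plan's own correlation of 0.50 and an assumption of equal SDs over time. For the other outcomes the direction is the same under equal SDs at any correlation below 1, but the size is unknown: 5% to 35% for correlations from 0.9 to 0.3.

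A reader might convert the 25% into participants (168/0.75 = 224) and conclude that the trial is under-sized, or could be smaller. That does not follow. The planned N fits a group-by-time interaction over five measurements, to which a single-contrast ratio does not transfer. The power figures in Step 5 rest on an assumed 0.5 SD difference and are illustrative.

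**What to change.** 1. In the Statistical analysis section, replace ANOVA on change by a linear model of the follow-up value (or of the change; the group estimate is the same) with the baseline of the same outcome as covariate. Alternatively, build baseline adjustment into the planned growth or mixed model and say how it enters.
2. Report baseline-adjusted group differences with 95% CI. Keep unadjusted change scores for description.
3. In the Assessment procedure section, define adjusted change scores in the same terms, or delete the phrase.
4. For step counts, use as covariate only tracker data recorded before any allocated intervention begins, and before randomisation if available. State the window.

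The sample size does not change. For questionnaire outcomes the cost is wording alone, since baselines are completed before randomisation. For step counts the team must first confirm that such data exist in every arm.

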## Discussion

Due to the novelty of using a combination of behavioral change strategies with acceptance and mindfulness-based therapy with a wearable device to promote a healthful lifestyle in the post-rehabilitation period, no well-defined hypotheses have been established about the possible contribution of this kind of intervention in comparison with the “gold standard” multidisciplinary treatment chronic conditions linked to obesity. With the development of mobile technology and brief clinical protocols, new interventions in the field of obesity and connected chronic pathologies have to be evaluated.

The mACTonHEALTH study is quite innovative for different reasons. First, the combination of single-case designs with an RCT is uncommon, particularly with medium-scale studies. Second, the use of a wearable device activity tracker both as a device for data collection measuring the primary outcomes and as a device to provide contingent feedback, assumed as one of the two independent variables, is unique. Third, directly combining brief ACT intervention and behavior modification strategies with mobile-tech implementation is another element of innovation. Furthermore, although ACT is becoming well studied in the traditional clinical context, large-scale application to both medical and natural settings has not largely occurred. Including in the assessment procedure directly collectable data as indicators of both physical and psychosocial health is unique. Also, the inclusion of objective physiological outcome measures constitutes an aspect of innovation in ACT research. Last, the study will focus on mediation mechanisms underlying the treatment’s success and present possible links to systematic models on psychological flexibility, a core process assessed in ACT research.

The particular experimental design, using both directly measured outcomes and psychometric measures, particularly aimed at checking for mediation and moderation effects, is also one of the limits of the study. The complex experimental design with multiple independent variables requires a higher number of participants and could weaken the findings if the conclusions are not clear. Another limit of the study is represented by the absence of a real group without activity trackers. This decision is due to the importance of gathering data only collectable by the trackers, but even when the wearables collect data in “silent” mode, without providing any feedback, participants wear the devices. Even assuming that the effect of simply wearing a similar device is small, we cannot check directly. Despite these limitations and others of lesser importance, such as the limited number of psychometric inventories and the relatively small sample size of each subgroup, the benefits of this experimental design seem to overcome the downsides. First of all, direct measure of movement and physical activity represents an essential outcome, rarely collected in such a sample. Moreover, despite the downside of a small sample, a similar method could be used as an efficient way to test different hypotheses and to control for interactions between variables.

To the best of the researcher’s knowledge, this study will be the first RCT to examine the effectiveness of combining contingent feedback provided with wearable devices with ACT-based interventions to make the lifestyle more healthful according to medical and behavioral prescription among obese patients. This study is also one of the first examples of a large implementation of multiple single-case designs with a continuous data collection, made possible through the implementation of wearable technology. Conducted in the context of clinical practice, this trial will potentially offer empirical support to alternative interventions to improve radical long-time change in life habits and consequently promote quality of life, reducing mortality and morbidity rates among an obese population. Furthermore, by virtue of its short duration, the program could potentially also be utilized for health promotion in non-hospitalization contexts and primary or secondary prevention of obesity and linked conditions.
